## 8. STUDY INTERVENTION

### 8.1 Identity of investigational products (treatment)

#### 8.1.1 Experimental intervention (treatment)

Group A: Dapagliflozin (DAPA);

Generic name: Dapagliflozin propanediol;

ATC code: A10BK01, [www.whooc.no](http://www.whooc.no);

Brand name: Forxiga ®;

Supplier and source: AstraZeneca AG;

Pharmaceutical form: Film-coated tablet;

Mode of administration: oral;

Color and appearance: Green, plain, and diamond shaped or yellow, biconvex, diamond shaped with number 10 debossed on 1 side and number 1428 on the other side;

Strength: 10mg/per tablet (Swissmedic number: 65176, [www.swissmedicinfo.ch](http://www.swissmedicinfo.ch));

#### 8.1.2 Control intervention (placebo treatment)

Group B: Placebo (PLA);

Supplier and source: AstraZeneca AG;

Pharmaceutical form: Film-coated tablet;

Mode of administration: oral;

Color and appearance: Look-alike placebo tablets are supplied in the same container/closure system. The placebo tablets contain lactose monohydrate, microcrystalline cellulose, magnesium stearate, and coating material (Opadry ® II).

#### 8.1.3 Packaging, labelling and supply (re-supply)

The investigational medicinal product (IMP) dapagliflozin (10mg/tablet) and corresponding placebo (= study drugs) will be supplied by AstraZeneca AG in packaging of identical appearance in form of primary packed unlabelled bottles, containing 35 tablets per bottle.

The Sponsor is responsible for study specific labelling of study drugs. For the present study, the blinding and labelling of study drug bottles will be executed by the hospital pharmacy (Kantonsapotheke Zürich, KAZ).

The randomisation list will be generated via the secuTrial software and forwarded in numeric form (01-100) by the CTC to the KAZ.

The investigational treatment pack will be a zip-pack kit containing 3 labelled bottles per each patient (labelling and secondary packaging performed by KAZ). Each patient kit has a 2-part label. A unique medication number is printed on each part of this label which corresponds to one of the 2 treatment arms. Investigator staff will identify the investigational treatment package(s) to dispense to the patient by contacting the IRT and obtaining the medication number(s).

Immediately before dispensing the package to the patient, investigator staff will detach the outer part of the label from the packaging and affix it to the source document (drug label form) for that patient's unique subject number from 01 to 100.

Medication labels will be in the local language and comply with the legal requirements of each country. They will include storage conditions for the investigational treatment but no information about the patient except for the medication number.

Upon receipt of the study treatment supplies, an inventory must be performed and a drug receipt log filled out and signed by the person accepting the shipment. It is important that the designated study staff counts and verifies that the shipment contains all the items noted in the shipment inventory. Any damaged or unusable study drug in a given shipment (active drug or placebo) will be documented in the study files.

Shelf life of the study drugs is long enough to cover the entire study period. In case of early expiry or

loss, the study drugs may be resupplied by AstraZeneca AG.

#### **8.1.4 Storage Conditions**

Investigational treatment must be received by a designated person at the study site, handled and stored safely and properly, and kept in a secured location to which only the investigator and designees have access. Upon receipt, all investigational treatment should be stored according to the recommended storage conditions and the instructions specified on the labels.

The study product is to be stored below 30°C (range: 15°C - 30°C) and should be kept away from light and moisture. Clinical supplies are to be dispensed only in accordance with the protocol.

For the present study, the investigational treatment will be stored at the study site ([name], room RAE E30) in a secured cupboard equipped with a temperature log system.

### **8.2 Administration of experimental and control interventions**

#### **8.2.1 Experimental and control intervention (placebo)**

AstraZeneca AG will supply the investigators with all study medications (dapagliflozin, placebo) required for the course of the study. Patients will be provided with medication packs containing study drug corresponding to their assigned treatment arm (A= DAPA or B= PLA), sufficient to last until the next scheduled visit.

The treatment regimen of dapagliflozin (1 tablet/day, dose: 10 mg, route: orally) is based on major trials (e.g. DAPA-HF) showing beneficial effects in HF-patients while being well-tolerated by patients with this treatment setting.

Dapagliflozin can be principally taken at any time and independent of meals according to the professional drug information sheet [81].

Patients will be instructed to take their study drug doses (1 tablet per day per oral) regularly in the morning to ensure a consistent and comparable treatment setting. The study drugs should be taken with water, with or without food.

The first IMP dose will be taken after the baseline testing is completed (Table 1). The patients will be instructed to take each daily dose separated by  $\geq 12$  hours from the previous one. If the patient misses taking any study drug dose, he/she should take it as soon as possible, unless it is less than 12 hours until the following scheduled dose.

In this case of  $< 12$  hours, the patient should skip the missed dose and return back to his/her regular study drug administration schedule.

All dosages prescribed and dispensed to the patient and all dose changes during the study must be recorded on the dosage administration record CRF.

### **8.3 Dose modifications**

The following situations require modifications of the study drug or other medications as described below:

- Symptomatic hypotension;
- Hypovolemia;
- Hypoglycemia;

For patients who are unable to tolerate the protocol-specified dosing scheme interruptions of study treatment are permitted in order to keep the patient on study drug. The following guidelines should be followed:

- Every attempt should be made to maintain patients at the target study drug dose level throughout the trial. If the patient does not tolerate the target study drug dose level, the investigator can adjust or stop concomitant background medications for co-morbid conditions to rectify the situation, before considering down-titration to the next lower study drug dose

level.

- For hypotension or dizziness, consideration should be given to reduce the dose of concomitant antihypertensive agents and non-antihypertensive agents that lower BP, or the dose of diuretic can be reduced.
- For hypovolemia consideration should be given to reduce the dose of concomitant diuretic agents and non-diuretic agents that lower volume status.
- For hypoglycemia (e.g. T2DM) consideration should be given to reduce the dose of concomitant anti-diabetic agents (e.g. insulin) and non-anti-diabetic agents that lower glucose levels.

If despite adjustment of concomitant medications the situation is not rectified, the investigator may consider discontinuation of study treatment.

## **8.4 Compliance with study intervention**

The investigator should promote compliance by instructing the patient to take the drug exactly as prescribed and by stating that compliance is necessary for the patient's safety and the validity of the study. The patient should be instructed to contact the investigator if he/she is unable for any reason to take the study drug as prescribed. Drug compliance will be tracked as described in section 8.8.

Non-adherence to study treatment will be defined as intake of less than 80% of the study drug dose as determined, using drug accountability logs.

Non-adherent patients will remain in the study and will be motivated to increase drug consumption and come to all study visits. Non-adherent patients will enter final data analysis in the intention-to-treat population but will not be analyzed in the per-protocol data set.

## **8.5 Data collection and follow-up for withdrawn participants**

Patients that withdraw from the study drug will be encouraged to participate in all regular study visits and assessments. Patients that withdraw consent will be included in the intention-to-treat analysis with the measurements that have been obtained until the withdrawal.

## **8.6 Trial specific preventive measures**

As stated, the study treatment will be taken on top of recommended therapy in heart failure. The trial specific preventive measures are adapted partially from the DAPA-HF trial [5] where the efficacy and safety were shown for both study arms in heart failure patients.

Dapagliflozin or placebo will be discontinued in case of:

- Pregnancy;
- Diabetic ketoacidosis (DKA);
- Fournier gangrene (FG);
- Severe recurrent genital infections (GI) and urinary tract infections(UTI);

A temporary discontinuation is permitted in case of:

- An acute, unexpected decline in the eGFR;
- Volume depletion, or hypotension (or to avoid these conditions);
- Hypoglycemia;

A subsequent restarting of treatment is intended, if possible.

The use of these trial specific preventive measures will be recorded in the eCRF.

## 8.7 Concomitant interventions (treatments)

The investigator should instruct the patient to notify the study site about any new medications he/she takes after the patient was enrolled into the study. All medications, procedures and significant non-drug therapies (including physical therapy and blood transfusions) administered after the patient was enrolled into the study must be recorded in the eCRF.

There are no specific or relevant concomitant care and interventions that are permitted (additional treatments) during the trial.

## 8.8 Study drug accountability

Investigational product supplies, which will be provided to the Sponsor-Investigator, must be kept in a secure, limited access storage area under the recommended storage conditions. The investigator must maintain accurate and adequate records including dates, lot number, quantities received and individual usage.

The study drug reconciliation will be performed at the study end to document drug assigned; drug consumed, and drug remaining. This reconciliation will be logged on the drug accountability form, and signed and dated by the study team.

Patients will be asked to return all unused investigational treatment and packaging at the end of the study or at the time of discontinuation of investigational treatment.

At the conclusion of the study, and as appropriate during the course of the study, the investigator will return all unused investigational treatment, packaging, drug labels, and a copy of the completed drug accountability log to the monitor.

## 8.9 Return or destruction of study drug

At the completion of the study, there will be a final reconciliation of drug shipped, drug consumed, and drug remaining. This reconciliation will be logged on the drug accountability form, signed and dated. Any discrepancies noted will be investigated, resolved, and documented prior to destruction of unused study drug on site. Drugs destroyed on site will be documented in the study files.

# 9. STUDY ASSESSMENTS

## 9.1 Study flow chart and table of study procedures and assessments

The study flow chart and table of procedures and assessments are depicted in the summary part of the protocol.

## 9.2 Assessments of outcomes

### 9.2.1 Assessment of primary outcome

The primary study outcome is the change in relative plasma volume status ( $\Delta$ PVS) from baseline to 12 weeks of dapagliflozin treatment on top of recommended therapy in comparison to placebo.

#### 9.2.1.1 *Assessment of relative plasma volume status*

The relative plasma volume status (PVS) has been proposed to have prognostic implications in heart failure patients and patients with cardiovascular diseases (see also 3.1.2). The PVS is defined as the % deviation of actual plasma volume (aPV) from the sex-dependent ideal plasma volume (iPV) as calculated by use of the Hakim-formula [36]:

$$1) \text{ PVS} = [(aPV - iPV) / iPV] \times 100\%;$$

The **actual plasma volume** (aPV) can be either estimated (ePV) by use of the following sex-

dependent formula or measured (mPV):

- 2)  $aPV = (1 - \text{hematocrit}) \times [a + (b \times \text{weight in kg})]$ ,  $a = 1530$  in males,  $a = 864$  in females and  $b = 41$  in males,  $b = 47.9$  in females;

The **ideal plasma volume** (iPV) can be calculated with the following sex-dependent simple formula:

- 3)  $iPV = c \times \text{body weight (kg)}$ , constant  $c = 39$  in males and  $c = 40$  in females;

In the present study, the PVS will be calculated using the optimized carbon monoxide rebreathing (OpCO) technique to measure the actual plasma volume ( $aPV = mPV$ ).

#### 9.2.1.2 Assessment of relative plasma volume status by use of the optimized carbon monoxide rebreathing technique

As stated, the relative plasma volume status will be calculated using the OpCO technique to measure the actual plasma volume (mPV) in heart failure patients by use of the Hakim formula as described previously (see 9.2.1.1):

$$PVS = [(mPV - iPV) / iPV] \times 100\%;$$

The OpCO technique is not yet established in clinical routine, however it is highly accurate and reliable method to measure total haemoglobin mass ( $Hb_{\text{mass}}$ ), the basis for calculation of intravascular volumes, e.g. plasma volume.

This is reflected by a reported low typical error (TE, 1-2%) and coefficient of variation (CV, 2.2%) for measuring  $Hb_{\text{mass}}$  [39-41].

Importantly, the OpCO technique has been recently shown to be safe and well-tolerated, and feasible to apply in heart failure patients with severe (LVEF < 30%) left ventricular dysfunction [42] but in contrast to radioactive isotope labelling techniques this technique does not expose patients to radiation.

Recent applications of the optimized CO-rebreathing technique to measure blood- and plasma volumes in patients with chronic kidney disease [43], dialysis-dependent kidney failure [44, 45] and patients with chronic liver disease [46] further emphasizes the brought ranged potential of this technique in the clinics.

A direct comparison between the measured plasma volume (mPV) assessed by OpCO technique and the estimated PV (ePV) assessed by the Hakim formula [36], which was used by others [10, 37, 93], has not yet been performed.

However, a recent study by Martens et al. [10] could demonstrate that the estimated PV in HF patients by use of a radioactive isotope (technetium-99) red blood cell (RBC) labelling technique correlated well with the estimated PV as calculated by the Hakim formula. In this context, Gore et al. [39] could show in a meta-analysis that the measurement error of CO-rebreathing is comparable (even lower) to radioactive RBC labelling technique.

Thus, the measured PV by use of OpCO technique (see formulas below) should reflect well the estimated PV based on the Hakim formula. Actually, it may reflect 'true' PV levels more accurately as it's also based on the direct measurement of volume independent total haemoglobin mass ( $Hb_{\text{mass}}$ , see formula below) and not solely on concentration dependent measures (e.g. Hct). Nevertheless, we will compare (correlate) the 2 different PV estimations with each other.

The underlying formulas used by us [45] and others [44] to calculate blood volume using OpCO technique are as follows:

- 1)  $nCO_{\text{absorbed}} = P_{\text{atm}} \times VCO_{\text{absorbed}} / (R \times T)$ ;
- 2)  $nHb_{\text{tagged}} = nCO_{\text{absorbed}} / 4$ ; (1 mole Hb binds 4 moles CO);
- 3)  $nHb_{\text{total}} = (nHb_{\text{tagged}} / \Delta HbCO) \times 100\%$ ;

- 4)  $Hb_{mass} = nHb_{total} \times 6.44 \times 10^4 \text{ g/mol}$  (= molar mass of Hb);
- 5)  $RBCV = Hb_{mass} \times Hct / Hb$ ;
- 6)  $BV = RBCV / Hct$ ;
- 7)  $PV \text{ (mPV)} = BV - RBCV$ ;

\*Hct should be corrected to whole-body Hct by the factor 0.91 [94].

Abbreviations:  $nCO_{absorbed}$ : amount of absorbed CO in moles after CO-rebreathing,  $P_{atm}$ : atmospheric pressure,  $VCO_{absorbed}$ : absorbed volume of CO in liters,  $R$ : gas constant (0.08206 l atm / (mol·K)),  $T$ : room temperature in Kelvin,  $nHb_{total}$ : total amount of Hb in moles,  $nHb_{tagged}$ : amount of tagged Hb in moles,  $\Delta HbCO$  (%): difference in carboxyhemoglobin (HbCO) measured in venous blood samples pre- and post CO-rebreathing,  $Hb_{mass}$  (g): total hemoglobin mass,  $RBCV$  (l): red blood cell volume,  $BV$ : blood volume,  $mPV$ : measured plasma volume;

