# %PVSopt: Percent of patients within proposed optimal PVS divergence interval for HF as defined by the combined divergence interval with the lowest reported hazard ratio (HR) for HF-hospitalization and mortality: -4% to -18% of iPV [9, 10]);

‡ Primary volume-related outcomes, § Primary vascular function-related outcomes, ° Other outcomes;

**Rationale:** The secondary outcomes are add-on study measures, which are directly or indirectly linked to the primary study outcome (PVS) and are supposed to be altered by dapagliflozin treatment according to scientific literature.

Thus, these parameters may help to provide a more detailed mechanistic insight into the effects of dapagliflozin treatment on volume status and vascular function as potential mediators of cardio-protection.

Additionally, the effects of dapagliflozin treatment on selected clinical outcomes will be also assessed and potential associations to measured functional parameters will be evaluated.

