### 9.2.1.3 Assessment of blood volume by use of the optimized carbon monoxide rebreathing technique

The blood volume (BV) will be determined by applying OpCO technique using a fully automated device (Detalo Instruments, Denmark) as illustrated (Fig. 10) with a very low typical error ( $\leq 1\%$ ).

Briefly, the participant will rest for at least 10 minutes in a supine position (resting phase, RP) prior to the start of the BV-measurements.

During this period a venous catheter (20G venflon, BD, USA) will be inserted into an antecubital vein and a first blood sample (2ml) will be taken shortly before the start of the rebreathing test to measure the percent carboxy hemoglobin (HbCO), the hemoglobin concentration (Hb), oxygen saturation (SaO2) and hematocrit (Hct) with a hemoximeter (ABL800, Radiometer, Denmark).

At the beginning of the rebreathing manoeuvre, the patient will breathe 100% of oxygen for 1 (flushing period, FP) through a mouth piece (mask), which is connected via a breathing filter and tubing system to the automated rebreathing device.

Thereafter, a bolus of 1 ml/kg of chemically pure carbon monoxide (CO, 99.997%, CO N47, Air Liquide, France) will be administered into the closed breathing circuit and the resulting gas mixture will be rebreathed for at least 2 to max. 10 minutes (rebreathing period, RBP) before patient will be disconnected from the rebreathing circuit.

The second venous blood sample will be taken from the same venous catheter 10 minutes after the start of the RBP to measure again the aforementioned parameters. The blood pressure and heart rate of the study participant will be assessed noninvasively before and after the BV-measurements by use of a non-invasive hemodynamic monitoring device (Finometer Midi, FMS, The Netherlands) or comparable NIBPD.

Duration of intervention: 20 min;

Main outcome parameters (units): PVS (%),  $Hb_{mass}$  (g), BV (ml), RBCV (ml), PV (ml),  $BV_{ratios}$  ();

[figure not shown]

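### The protocol does not say which haematocrit the 0.91 correction governs; read literally it shifts the level of PVS, and %PVSopt applies an interval reported for calculated PVS to measured PVS.

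*Protocol*

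**What the plan says.** Section 9.2.1.2 gives three steps from haemoglobin mass to plasma volume: RBCV = Hbmass × Hct / Hb (equation 5), BV = RBCV / Hct (equation 6) and PV = BV − RBCV (equation 7). A starred note below them reads "Hct should be corrected to whole-body Hct by the factor 0.91". In the text at hand no haematocrit in equations 5 to 7 carries a matching star.

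Section 9.2.1.3 takes haemoglobin "and hematocrit (Hct) with a hemoximeter (ABL800, Radiometer, Denmark" from the same venous sample. No correction of haemoglobin is mentioned.

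Section 9.2.1.1 fixes the trial's variable: "In the present study, the PVS will be calculated using the optimized carbon monoxide rebreathing (OpCO) technique to measure the actual plasma volume". Its equation 2, based on haematocrit, weight and sex, gives the alternative, estimated plasma volume.

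Section 5.2 lists %PVSopt as a secondary outcome: "Percent of patients within proposed optimal PVS divergence interval for HF", with limits of −4% and −18% of ideal plasma volume taken from references 9 and 10. Section 9.2.1.2 attributes the haematocrit/weight estimate to reference 10, among others, and states that it has not yet been compared directly with the CO-rebreathing measurement. In the trial, "we will compare (correlate) the 2 different PV estimations with each other".

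**The concern.** The plasma volume behind the primary variable needs one definition. The unscoped note permits several, and they give different levels of PVS.

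Applying the factor to every haematocrit is also incoherent. In equation 5, Hct/Hb is the reciprocal of the mean corpuscular haemoglobin concentration, a property of the red cell. The body-to-venous ratio does not alter it. Scaling the venous haematocrit by 0.91 but leaving the venous haemoglobin from the same sample unscaled raises the implied concentration by 1/0.91 = 1.099. Blood volume, the quantity a whole-body correction is meant to adjust, then receives no correction.

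The level of PVS matters in two places. Section 11.1 defines improvement as movement towards ideal plasma volume (PVS = 0), and %PVSopt counts patients inside a fixed window 14 points wide. A window reported on one scale and applied to another is open to any offset between the methods, whatever is decided about the 0.91.

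**Working it through.** The protocol contains no worked plasma volume or PVS, so there is no stated figure to reproduce for the formula itself. The sample size does reproduce: 128 × (1 − 0.6²) = 81.92, against 81.9 in section 11.2. It does not depend on this point.

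**Placement of the factor.** Write V = Hbmass/Hb and H = venous Hct.

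| Factor placed in | RBCV | BV | PV | PV/V at H = 0.40 (assumed) |
|---|---|---|---|---|
| every Hct | 0.91VH | V | V(1 − 0.91H) | 0.636 |
| equation 6 only | VH | V/0.91 | V(1 − 0.91H)/0.91 | 0.699 |
| nowhere | VH | V | V(1 − H) | 0.600 |
| equation 5 only | 0.91VH | 0.91V | 0.91V(1 − H) | 0.546 |

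The first row divided by the second is exactly 0.91 for RBCV, BV and PV, at any H. Against no correction, the every-Hct plasma volume is higher: 0.636/0.600 = 1.06.

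**Effect on PVS.** Because PVS = (PV/iPV − 1) × 100,

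PVS(every Hct) = 0.91 × PVS(equation 6 only) − 9.

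So 0% becomes −9.0%, +2% becomes −7.2% and −10% becomes −18.1%. In reverse, the −4% to −18% window applied to the every-Hct values covers 0.96/0.91 − 1 = +5.5% to 0.82/0.91 − 1 = −9.9% on the equation-6-only scale.

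**Effect on %PVSopt.** The protocol gives no PVS distribution, so normal distributions on the equation-6-only scale are assumed.

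| Mean PVS | SD | In window, equation 6 only | In window, every Hct |
|---|---|---|---|
| +5 | 8 | 13% | 49% |
| 0 | 8 | 30% | 65% |
| −10 | 8 | 62% | 47% |
| +5 | 12 | 20% | 41% |
| 0 | 12 | 30% | 47% |
| −10 | 12 | 44% | 40% |

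Both the size and the direction of the shift depend on where the patients lie.

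**Effect on the primary comparison.** The constant −9 drops out of a change, and the factor 0.91 multiplies estimate and standard error alike. An ANCOVA on one simulated trial of 80 patients gave a difference of −6.86 on one scale and −6.24 on the other (ratio 0.91), with t = −4.037 and p = 0.00013 on both. The same algebra applies to the planned mixed model, provided one rule is used at every visit.

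**One illustrative patient.** Assume a man of 80 kg with Hbmass 700 g, Hb 130 g/l and Hct 0.40. Then V = 700/130 = 5.385 l and iPV = 39 × 80 = 3,120 ml.

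- every Hct: 3.425 l, PVS +9.8%
- equation 6 only: 3.763 l, PVS +20.6%
- no correction: 3.231 l, PVS +3.6%
- equation 5 only: 2.940 l, PVS −5.8%
- equation 2: 0.60 × (1530 + 41 × 80) = 2,886 ml, PVS −7.5%

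This patient is inside the window by equation 2 but outside it under the first three readings. The values are invented and show only that the choice can decide the classification.

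**Correlation as a check.** Replacing x by 0.91x − 9 leaves a correlation coefficient unchanged. An offset or proportional difference of this kind would be invisible to it, yet that is what decides whether a fixed cut-off can be carried over.

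**The case against.** The strongest reply is that the note is unscoped, not misapplied. A star needs an anchor, and one on equation 6 may have been lost when the PDF was read; the protocol would then already say what is asked for. The device is automated, and the formulas are attributed to earlier publications that are not at hand, so what will actually be computed is unknown. This stands. A reader might infer that the trial's plasma volumes are shown to be 9% too low. The documents do not support that: the 9% is the gap between two readings, and against no correction the every-Hct value is higher.

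A reader might also infer damage to the primary test, its power or the sample size. Between the every-Hct and equation-6-only readings there is none.

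On the interval, the protocol openly says that the methods have not been compared, gives reasons for expecting similarity, plans a comparison and calls the interval proposed. Disclosure does not justify the transfer, and the supporting evidence it cites is itself correlation and measurement error. It is fair to add that use of equation 2 by both source studies is not established. For reference 9 the protocol offers only the word 'calculated' in its title. For reference 10 it rests on a citation string that also credits the formula to reference 93, for which section 3.1.2.1 describes a different formula.

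Finally, it is tempting to say that the planned correlation will be inflated because both estimates use haematocrit and share the same ideal plasma volume. That is not shown. Section 9.2.1.2 correlates plasma volumes, which are not divided by ideal volume; section 3.1.2.2 mentions PVS, and the effect of that division can go either way. An analysis plan not seen here may also specify an agreement analysis.

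**Conclusion.** The concern holds as two separate points.

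First, the scope of the 0.91 factor is not stated. On the literal, every-Hct reading, blood volume loses the correction, RBCV, BV and PV are each 0.91 of the equation-6-only values, and PVS falls to 0.91 × PVS − 9 points. This size is conditional on that reading and on taking equation 6 only as the reference, which is the coherent choice because haemoglobin and haematocrit in equation 5 come from the same venous sample.

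Second, whatever the answer on the factor, %PVSopt transfers an interval reported for calculated PVS to measured PVS without agreement data, and the check named in the protocol cannot reveal an offset.

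The exposure is absolute PVS, the blood volume profile and %PVSopt, all of which can shift materially. The proportions in the window rest on assumed distributions. The change should be made, but it does not threaten the primary between-group test.

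**What to change.** 1. In section 9.2.1.2, write RBCV = Hbmass × Hct/Hb with uncorrected venous values, BV = RBCV/(0.91 × Hct) and PV = BV − RBCV. Confirm that the device output uses the same rule, and recalculate from the raw values if it does not.
2. In section 5.2, report %PVSopt also from equation 2, the calculated scale, alongside the CO-rebreathing version.
3. In sections 3.1.2.2 and 9.2.1.2, add bias and limits of agreement (Bland-Altman) between measured and estimated plasma volume, rather than correlation alone.

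The cost is wording and recalculation. Haemoglobin mass, haemoglobin, haematocrit, weight and sex are already collected, and the sample size does not change.
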